### Sample size

A sample size of 1338 participants (randomised to one of three groups of 446 participants) will be needed to detect a moderate effect size of 30 daily counts per minute (CPM) in a two-sided test, at a power of 80% and an α of 0.05, a common standard deviation of 139 of the mean and a 24% dropout rate. A change of 30 CPM is considered a measurable moderate effect size in this population, assessed with ActiGraph GT3X+, and 139 is the standard deviation for CPM found in the literature [37]. The present sample size allows estimation of overall efficacy.

Sample size computations were conducted with online software GRANMO (http://www.imim.es/ofertadeserveis/software-public/granmo/; last accessed on 21/7/2014).

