**Fig. 2 Fig2:**
[figure not shown]
SPIRIT figure

Personal information regarding age, gender, marital status, living arrangement, educational background, medical conditions, and smoking and alcohol habits will be collected at baseline.

The costs of the interventions (ERS, SMS and the CG intervention) will be also collected by a structured questionnaire.

Primary outcomes of the study include: (1) SB as sitting time and the number of minutes spent in activities requiring ≤ 1.5 MET, as objectively measured by hip worn ActiGraph® accelerometer, and in addition with ActivPal® (used in Barcelona and Ulm) and Axivity® (used in Odense and Belfast) accelerometers worn on the thigh, and as self-reported according to the Patient-centered Assessment and Counseling for Exercise (PACE), Sedentary Behavior Questionnaire); and (2) physical activity as daily CPM and intensity of exercise performed, as measured by ActiGraph®. Primary and secondary measures will be collected at the four time points. For an overview of primary and secondary outcomes, outcome measures, instruments and assessment time points, see Table 2.

**Table 2 Tab2:** Overview of outcomes, outcome measures, instruments and assessment time points

Outcomes	Outcome measures	Instrument	Assessment time point^a^
Personal information	Age, gender, civil status, living arrangement, educational background, medical conditions, and smoking and alcohol habits.	Primary care records Self-report	T0
Primary outcomes			
Sedentary behaviour	Sitting time and the number of minutes spent in activities requiring ≤ 1.5 Metabolic Equivalent Tasks.	Actigraph® ActivPal® Axivity® Sedentary Behavior Questionnaire	T0, T1, T2, T3
Physical activity	Daily counts per minute and intensity of exercise, and daily step counts.	Actigraph®	T0, T1, T2, T3
Secondary outcomes			
Physical function	General function Aerobic capacity Static balance	SPPB 2-minutes’ walk test Unipedal stance	T0, T1, T2, T3
Muscle function	Handgrip strength	Takei analogue Hand Grip Dynamometer	T0, T1, T2, T3
	Mean strength and power with concentric contraction of isoinertial movement performing 3 exercises: (a) 30-s chair stand rise; (b) five repetitions of arm curl with both hands using a 2-kg and 4-kg weight; and (c) four counter-movement jumps.	Linear encoder	
Health economics’ related outcomes	Use of sport services, and use of health and social services, medications, number of falls.	Interview	T0, T1, T2, T3

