### Data and statistical analysis

The full analysis set will follow the intention-to-treat principle and will include all randomised participants for whom a baseline assessment is conducted, regardless of later temporary or permanent loss to follow-up, withdrawal or drop-out of the study.

The study hypothesis will be tested with mixed linear models with repeated measures, to assess changes in main outcomes (SB and CPM) over time (T0 to T3) and between-study arms. A diagonal matrix design will be considered for the within-participants covariance matrices (covariance structure for repeated measures factors). Fixed effects in the analyses will be treatment group and country (study site), the latter based on its relevance as proxy for intervention and cultural differences. Random effects may be considered for the ERS + SMS group and ERS group, to take into account within-study clustering. A diagonal matrix design will be considered for the between-participants covariance matrices (covariance structure for random factors). The between-participants correlations induced by randomisation by centre and the clustering of cohabiting individuals will be taken into account in the models. Further testing of the study hypotheses will be conducted through covariance analyses, including in the model relevant covariates (age, gender, BMI, SPPB level and frailty), and effect modifiers.

Secondary analyses will be conducted to explore changes over time in the relative efficacy of the interventions. Mixed linear models with repeated measures will be built to assess changes over time between intervention groups in main and secondary variables, at baseline (T0) and T1, T2 and T3. Interaction terms between treatment and time will be considered to test for differences over time between treatments.

A sensitivity analysis will be conducted, restricted to the ‘per protocol’ dataset, comprising all participants with no protocol violations and complete (e.g. no missing data) measurements for the primary variables for all study assessments (baseline, end of treatment, first follow-up, second follow-up). A second sensitivity analyses will be conducted for any primary variable with a substantial number of missing values (higher than 5%), imputing missing data by the ‘last observation carried forward’ method.

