No subgroup analyses are planned in advance. Any subgroup analysis conducted will be treated with caution and output will be treated as exploratory rather than definitive. Missing data will be imputed through a multiple imputation approach, imputing missing values with the corresponding average values from the set of participants in the control group in the same country as the participant, matched for age, gender, baseline PA and baseline SPPB score.

Two-sided tests of statistical significance will be used in all statistical analyses. Estimates of the size of treatment effects will be presented together with confidence intervals, in addition to significance tests. Significance levels will be set to a 5% level, applying the Bonferroni correction to adjust for type I error criteria. All analyses will be performed with SPSS version 20 or Stata version 12.

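### Baseline CPM and sedentary time enter the mixed model only as responses, so the plan uses them inefficiently; for CPM, baseline adjustment would gain about 2 to 18 power points, depending on an unstated correlation

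*Protocol article*

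**What the plan says.** All places are in the Protocol article.

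- **When baseline is measured.** The outcome assessment section says: "Primary and secondary measures will be collected at the four time points". Under Randomisation and blinding, allocation follows the baseline assessment. T0 values of both primary outcomes are therefore pre-randomisation measurements.
- **Primary model.** Data and statistical analysis specifies a repeated-measures mixed linear model of sedentary behaviour and CPM from T0 to T3, so T0 is one of the responses. On the model terms it says: "Fixed effects in the analyses will be treatment group and country (study site". A diagonal within-participant covariance is to be considered. No constraint gives the arms the same baseline mean.
- **Covariance analyses.** These are described as "including in the model relevant covariates (age, gender, BMI, SPPB level and frailty), and effect modifiers". Baseline CPM and baseline sedentary time are not named.
- **Treatment-by-time terms.** These are to be considered, in the paragraph on secondary analyses.
- **Only other use of baseline activity.** The imputation procedure uses control participants "matched for age, gender, baseline PA and baseline SPPB score", so the authors regard baseline activity as informative about later activity.

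**The concern.** The baseline value of an outcome is usually the best single predictor of its later value. Having T0 in the response vector recovers that information only under two conditions: the visits are allowed to correlate, and the arms are held to a common baseline mean, as randomisation justifies. The plan states neither. Two readings of its model remain, and neither uses the baseline well.

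- **Literal reading** (treatment and country, no treatment-by-time term). The treatment effect is an average over all four visits, including one that precedes treatment. Chance baseline imbalance passes into the estimate, and a real effect is diluted.
- **Treatment-by-time reading.** The month-22 effect is a difference in change from baseline. This subtracts the whole baseline difference, where only the fraction given by the correlation should be removed.

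At stake is precision in a trial sized at 80% power for 30 CPM against an SD of 139, before the Bonferroni correction that the plan also applies.

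**Working it through.** **1. Inputs (Sample size section).** "A sample size of 1338 participants (randomised to one of three groups of 446 participants"; "to detect a moderate effect size of 30 daily counts per minute (CPM) in a two-sided test"; power 80% and alpha 0.05; "a common standard deviation of 139 of the mean and a 24% dropout rate".

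**2. The plan's own figure.** Evaluable n per arm = 2 × (1.960 + 0.842)² × 139² / 30² = 337. Allowing for dropout, 337 / 0.76 = 444, against 446 stated, so the figure reproduces. It describes two arms compared at one visit with no use of baseline. With 446 × 0.76 = 339 per arm, SE = 139 × √(2/339) = 10.68 CPM and power = Φ(30/10.68 − 1.96) = 80.2%.

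**3. Three ways to treat baseline.** Let ρ be the correlation between T0 and follow-up, with equal SDs. Relative to the unadjusted follow-up comparison, the variance factor is:

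- unadjusted: 1
- change score: 2(1 − ρ)
- baseline-adjusted: 1 − ρ²

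Because 2(1 − ρ) − (1 − ρ²) = (1 − ρ)² ≥ 0, the change score is never more precise than adjustment. For ρ below 0.5 its factor exceeds 1, so it is less precise than ignoring baseline.

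**4. Power for CPM.** SE = 10.68 × √factor. At ρ = 0.5 the adjusted SE is 10.68 × √0.75 = 9.25, and power is Φ(30/9.25 − 1.96) = 90.1%. The document gives no ρ, so a range is shown. Gains are taken before rounding.

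| Assumed ρ | Unadjusted | Change score | Adjusted | Gain over unadjusted | Gain over change score |
|---|---|---|---|---|---|
| 0.3 | 80.2% | 66.1% | 83.8% | 3.6 | 17.7 |
| 0.4 | 80.2% | 72.7% | 86.6% | 6.3 | 13.8 |
| 0.5 | 80.2% | 80.2% | 90.1% | 9.8 | 9.8 |
| 0.6 | 80.2% | 88.1% | 94.0% | 13.7 | 5.8 |
| 0.7 | 80.2% | 95.2% | 97.6% | 17.4 | 2.4 |

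**5. What a chance baseline difference of 10 CPM leaves in the estimate** (illustrative; ρ = 0.5 between all visits, equal visit weights):

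- literal model, mean of T0 to T3: 10 × (0.25 + 0.5 × 0.75) = +6.2 CPM
- T3 alone: 10 × 0.5 = +5.0 CPM
- T3 minus T0: 10 × (0.5 − 1) = −5.0 CPM
- baseline-adjusted: 0

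**6. Dilution in the literal model.** If the effect is 30 CPM at each of T1, T2 and T3, averaging in T0 gives 30 × 3/4 = 22.5 CPM. With a correct SE of 10.68 × √((1 + 3 × 0.5)/4) = 8.44, power is Φ(22.5/8.44 − 1.96) = 76.0%. At ρ = 0.7 it is 66.8%.

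**The case against.** A reader might infer that chance baseline imbalance is left uncorrected throughout. The document does not support that. T0 is a response and treatment-by-time terms are to be considered, and that contrast does act on a baseline difference, though it over-corrects. Imbalance passes straight through only in the literal model.

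A reader might also take the loss to be a settled 10 points. It is not. That figure holds at ρ = 0.5, where the two comparators coincide. Elsewhere the gains run in opposite directions and can be as small as 2 to 4 points. The calculation is also a single-visit approximation, not the planned repeated-measures model. It takes standard errors as correct: a strictly diagonal model would report 139 × √2 × √(2/339) = 15.10 for the T3 minus T0 contrast, where the true value at ρ = 0.5 is 10.68.

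Further points stand:

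- The diagonal structure is only to be considered, and the covariate list is not called exhaustive.
- The analysis set requires that a baseline assessment took place, not that valid T0 accelerometer data exist.
- Randomisation keeps the unadjusted and change contrasts unbiased, and the planned 80% does not depend on a baseline covariate. This is a matter of efficiency more than validity.

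One might add that model terms belong in the SAP. But this article names the fixed effects, a covariance structure and the covariates, so the point concerns a stated method. None of these objections supplies a reading in which baseline is used efficiently.

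**Conclusion.** The point holds in a limited form. As described, the plan uses T0 CPM and T0 sedentary time only as responses, with no baseline covariate, no common-baseline constraint and a diagonal covariance under consideration. For CPM at alpha 0.05, baseline adjustment would gain about 4 to 17 points over an unadjusted comparison and about 18 to 2 points over a change score as ρ goes from 0.3 to 0.7. These figures rest on an assumed ρ, equal SDs at baseline and follow-up, and one visit.

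The Bonferroni divisor is not stated. If it were three, the same inputs give 66.1% unadjusted and 80.2% adjusted at ρ = 0.5. Nothing can be computed for sedentary time, because the document gives neither an SD nor a target difference for it. The change is a nearly free improvement, not the repair of an invalid test.

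**What to change.** In Data and statistical analysis, specify one of the following for each primary outcome, and likewise for secondary outcomes measured at T0:

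1. **Preferred.** Keep T0 in the response vector, with visit and treatment-by-visit terms, arms constrained to a common baseline mean, and a covariance that allows visits to correlate (for example unstructured). Participants without valid T0 accelerometer data are retained.
2. **Alternative.** Model T1 to T3 with the T0 value of the same outcome, and its interaction with visit, as covariates, and state a rule for missing T0.

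In either case keep country as a fixed effect, name the month-22 contrast as the main one, in line with the Study design section, and add the baseline value of the outcome to the covariates of the covariance analyses.

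The cost is wording and a few degrees of freedom, with no new data or participants. Trial status reports that no participant had completed the intervention at submission, so at that stage the change could be prespecified without sight of follow-up results.

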Primary care is a key setting for the promotion of PA. The most common model of PA promotion in primary care involves exercise referral schemes (ERS), whereby a general practitioner or another member of the primary care team (e.g. physiotherapist, nurse or pharmacist) identifies and refers insufficiently active individuals to a third-party service (often a sports centre or leisure facility) to conduct an exercise program [21, 22]. Despite recent studies showing the health benefits of such programs, most studies also demonstrate that such gains are rarely sustained [21]. Recent guidelines also advocate the use of established behavioural change techniques (BCTs) to promote increased levels of PA [23]. Among those, self-management strategies (SMSs) may successfully improve involvement in exercise in specific populations, increasing levels of daily PA, enhancing quality of life, improving mental health, producing greater confidence and increasing power to act [24].

Research focusing on interventions to reduce SB has only begun to emerge in the last five years and there have been few studies conducted in older adults. Recent studies targeting reduced SB in this population have included BCTs such as goal setting, instruction on how to perform the behaviour, self-monitoring and feedback of behaviour, prompts/cues and restructuring the physical environment [25–29]. Moderate quality evidence indicates that specific interventions have the potential to reduce SB in older adults [30]. These findings are supported by systematic reviews focusing on adults [31–33]. As far as we know, no previous studies have assessed the effects of an exercise-based intervention enhanced by SMSs addressing both increased daily PA and a reduction of SB in older adults.

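### The only imputation-based sensitivity analysis is last observation carried forward, which assumes persistence to month 22 in those lost and whose bias changes size and sign with dropout timing

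*Protocol article*

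**What the plan says.** The protocol article, under Data and statistical analysis, sets out three ways of dealing with missing primary data.

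- **Main rule.** It is labelled multiple imputation and described as "imputing missing values with the corresponding average values from the set of participants in the control group in the same country as the participant", with further matching on age, gender, baseline activity and baseline SPPB.
- **First sensitivity analysis.** A per-protocol set, "comprising all participants with no protocol violations and complete (e.g. no missing data) measurements for the primary variables for all study assessments".
- **Second sensitivity analysis.** For any primary variable with more than 5% missing, "imputing missing data by the ‘last observation carried forward’ method" (LOCF).

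The Sample size section plans for "a 24% dropout rate". Study design makes month 22, which is 18 months after the intervention ends, the main assessment; the earlier follow-up visits are at months 4 and 16. On exercise referral schemes, the Background states that "most studies also demonstrate that such gains are rarely sustained".

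**The concern.** The trial asks whether activity gains last. For a participant last seen at month 4, LOCF answers by assumption: the value at the end of the exercise programme becomes the month-22 value. For one last seen at month 16, that visit's value is moved forward six months. Persistence is thus assumed in exactly the people in whom nobody observed it, against the protocol's own statement that such gains tend to be lost. The carried values also enter the model as if measured, so the uncertainty about them is not counted.

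LOCF is the only sensitivity analysis that imputes anything. If it agrees with the main result, the agreement may be read as evidence of robustness to dropout. LOCF cannot supply that evidence, because its error depends on when people left and how the effect moved afterwards.

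**Working it through.** **Inputs from the Sample size section:** difference 30 CPM, SD 139, 446 per arm, 24% dropout, two-sided 5%, power 80%. **Assumptions, not in the document:** the course of the effect over time, the timing of dropout, 24% missing at month 22 in each arm, and dropout unrelated to outcome.

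**1. The plan's own figure.** n per arm = 2 × (1.960 + 0.842)² × 139² / 30² = 337. Allowing for dropout, 337 / 0.76 = 444, against 446 stated. With 446 × 0.76 = 339 completers per arm, power is 80.2%. The sample size reproduces and is not in question.

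**2. Will LOCF run?** Planned dropout is 24% and the trigger is 5%; 24 / 5 = 4.8, so the trigger should be met with room to spare.

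**3. Bias formula.** Let d1, d2 and d3 be the true between-arm differences at months 4, 16 and 22, and s0, s1 and s2 the shares of dropouts last seen at baseline, month 4 and month 16. Randomised arms do not differ at baseline in expectation, so

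LOCF estimate = 0.76 × d3 + 0.24 × (s0 × 0 + s1 × d1 + s2 × d2)

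Bias = 0.24 × (s1 × d1 + s2 × d2 − d3)

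The bias is positive only when the average carried difference exceeds the true month-22 difference.

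**4. Results (bias in CPM).**

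| d1, d2, d3 | All lost before month 4 | Last visits spread equally | All last seen at month 4 |
|---|---|---|---|
| 30, 15, 0 (full fade) | 0 | +3.6 | +7.2 |
| 30, 20, 10 (partial fade) | −2.4 | +1.6 | +4.8 |
| 30, 22.5, 15 (partial fade) | −3.6 | +0.6 | +3.6 |
| 30, 30, 30 (sustained) | −7.2 | −2.4 | 0 |
| 0, 15, 30 (emerges late) | −7.2 | −6.0 | −7.2 |

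Example, first row, equal spread: 0.24 × (30/3 + 15/3 − 0) = 0.24 × 15 = 3.6.

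**5. What this does to a test when the true month-22 difference is zero.** Treat the filled data as 446 observed values per arm in a simple month-22 comparison. SE = 139 × √(2/446) = 9.31. The rejection rate is Φ(bias/SE − 1.96) + Φ(−bias/SE − 1.96):

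- bias +3.6: bias/SE = 0.39, rejection about 7%;
- bias +7.2: bias/SE = 0.77, rejection about 12%.

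Both use an unadjusted 5%. The protocol applies Bonferroni without naming the family. If it covers three pairwise contrasts (an assumption), the nominal level is 0.05/3 = 1.7% and the 12% becomes about 5.3%.

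**6. The main rule for comparison.** If dropouts receive control-arm averages, the estimate is 0.76 × d3. This is unbiased under full fade, but a sustained 30 CPM becomes 22.8 (bias −7.2).

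**The case against.** A reader might infer that LOCF always favours the intervention. The documents do not support that. Participants lost before month 4 carry a baseline value, which adds no arm difference. With partial fading the bias can reach −3.6 CPM in the cases run. For ERS + SMS against ERS alone the sign may well reverse: both arms receive the same 16-week programme, and the SMS telephone calls run to week 30 (Table 1). If ERS alone fades while SMS sustains activity, the arms separate after month 4 and LOCF understates the difference. This objection stands, and the point is worded accordingly.

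The +7.2 CPM and 12% figures are the extreme case: everyone last seen at month 4 and a complete fade. A month-4 effect larger than 30 CPM would scale the bias up, but nothing in the document supports one. A rejection rate is also only an illustration, because the plan does not declare efficacy on a sensitivity analysis.

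A reader might also infer that none of the planned analyses departs from missing at random. That goes too far. LOCF is itself a crude, fixed departure, and filling in control averages is a reference-type assumption. What remains is that each fixes a single assumption and none varies it.

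Nor would disagreement between LOCF and the main rule be meaningless. Where the two err in opposite directions they act as rough bounds. They do not bound the truth in general: with a late-emerging effect or early dropout, both understate it.

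**Conclusion.** The point holds in this limited form. LOCF is a prespecified choice, not a gap that a separate analysis plan might fill, and it is expected to run. Against control, with an assumed 30 CPM month-4 effect, full fade and 24% missing, its bias runs from 0 to +7.2 CPM (7.2/30 = 24% of the design difference), with +3.6 CPM under equal spread of last visits. Under partial fade or a late-emerging effect it can be negative. Dropout timing and the course of the effect are assumptions, since the document gives neither.

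A check whose size and sign depend on those unknowns cannot show whether the month-22 result is robust to dropout. The per-protocol complete-case analysis does not fill the gap, because it leaves out everyone with missing data. The consequence is confined to a sensitivity analysis; the primary estimate and the sample size are unaffected.

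**What to change.** In Data and statistical analysis, replace LOCF with delta-adjusted multiple imputation: impute under missing at random as the base, shift the imputed values by a delta set separately for each arm, search over delta for the point at which the month-22 conclusion changes, and pool with Rubin's rules. Report the tipping point for each pairwise contrast, since the plausible direction differs between exercise against control and ERS + SMS against ERS alone.

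If a control-based assumption is also kept, carry it out as reference-based multiple imputation with properly drawn values, not by filling in control averages. On its own this would largely repeat the assumption in the main rule and mainly improve the variance; the delta analysis is what is new.

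The cost is revised analysis wording and a little more analysis work. No visits, data or participants are added. The change should be made before unblinding.

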### Randomisation and blinding

During the first meeting, a researcher will explain the trial to interested individuals, give them an information sheet about the study and obtain their written informed consent (see Additional file 1). Participants will then be scheduled for the baseline testing session. After the baseline assessment, each participant will be centrally randomised to one of the three study groups (e.g. ERS + SMS, ERS or the control group), using a computer-based random-block randomisation scheme, clustering by couples when cohabitees wish to be enrolled together. Concealed randomisation will be conducted centrally at FSiE, after each participant has been included in the study, assigned an identification code and has completed the study baseline assessment.

The trial has an open design with blind assessment of outcomes. Researchers conducting the baseline assessments will be blind to group allocation. The statistician will also be blind to group allocation until completion of the statistical analysis. Participants will be asked not to reveal group allocation when undergoing follow-up measurements, as researchers conducting follow-up measurements will be blind to group allocation. To assess the extent to which blinding has been preserved, researchers will record the number of cases in which allocation was revealed.

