As for the outcomes, self-reported health-related quality-adjusted life-years (QALYs) will be obtained using the EQ-5D-5 L EuroQol [45, 46] instrument as well as the newly developed capabilities measure of outcomes for older people, the ICECAP-O instrument [47]. The multinational aspect of the analysis requires the use of country-specific tariffs, which reflect country-specific differences in health perceptions and preferences and might severely affect Cost-Utility analysis [48–50]. When available, country-specific tariffs will be used to evaluate health outcomes.

The within trial analysis will explicitly take the multi-country nature of the SITLESS trial into account, by using appropriate methodologies as suggested by the most recent literature and best practices. The multi-national feature of the SITLESS trial implies a hierarchical structure of the data and unobserved heterogeneity between clusters that needs to be adequately modelled with appropriate statistical and econometric techniques [51, 52]. Following best practice approaches [53–55] a multiple imputation procedure using chained equations (MICE) will be used to impute missing data separately for each arm of the trial.

Within-trial results will be reported and presented as an incremental cost-utility ratio with the joint distribution of cost/utility pairs being represented on the cost-effectiveness plane and with a cost-effectiveness acceptability curve (CEAC) [56].

The within-trial economic evaluation results will be combined with evidence from the literature linking short-term outcomes with longer-term outcomes to produce a long-term cost-effectiveness decision analytic model. A Markov model will be the envisaged analytic tool to evaluate population health interventions and to examine outcomes over an extended period of time and it will be developed alongside Frew et al. [57] and Roux et al. [58]. However, given that such long-term impacts are likely to be reliant on some untestable assumptions, the model will comprise a detailed sensitivity analysis to explore how cost-effectiveness will vary within all realistic ranges of costs and outcomes.

As recommended by the UK’s NICE guidance on economic evaluation of population health interventions an annual population health discount rate of 1.5% will be applied to costs and outcomes.

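### Missing values in every arm are filled with control-group averages under the name of multiple imputation; unless dropouts revert to control level, this dilutes the effects and can distort ERS+SMS versus ERS

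*Protocol article*

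**What the plan says.** All statements are in the protocol article.

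- **Data and statistical analysis, main rule.** The method is called multiple imputation and is then defined as "imputing missing values with the corresponding average values from the set of participants in the control group in the same country", with matching on age, gender, baseline activity and baseline SPPB. It is not limited by arm, outcome, visit or reason for missingness, and it is not labelled a sensitivity analysis. The full analysis set keeps everyone randomised with a baseline assessment, including those lost only temporarily. The hypothesis is tested with a repeated-measures mixed model. How the fill and the model combine is not stated.
- **Same section, checks.** One sensitivity analysis is per protocol with complete data. The other is last observation carried forward (LOCF): "A second sensitivity analyses will be conducted for any primary variable with a substantial number of missing values (higher than 5" per cent).
- **Economic evaluation.** Chained equations "will be used to impute missing data separately for each arm of the trial".
- **Sample size.** One overall dropout rate of 24% is given, not split by arm or visit.
- **Background.** On exercise referral, "most studies also demonstrate that such gains are rarely sustained".

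**The concern.** The label and the procedure do not agree. Multiple imputation draws several values from a predictive distribution and carries their spread into the standard error. An average of matched controls is one number per participant.

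The choice of donors matters more. Everyone missing from ERS or ERS+SMS is given a control outcome. This includes a participant who completed the programme, was measured at months 4 and 16 and missed only month 22, because the matching uses baseline variables alone. Any benefit that such people kept is removed from the estimate. Both active arms are filled from a third arm, so the comparison of ERS+SMS with ERS, which is the trial's central question, depends on the two dropout rates as well as on the two effects.

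EQ-5D is a secondary outcome in Table 2 and also the source of the QALYs. Its missing values would therefore be handled under two incompatible assumptions in one trial.

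**Working it through.** **Inputs.** From Sample size: SD 139 CPM, α 0.05, power 80%, 24% dropout, 446 per arm, and the target: "detect a moderate effect size of 30 daily counts per minute (CPM) in a two-sided test". Unequal dropout rates, covariate R² and number of matched controls are assumptions, marked where used.

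**1. The plan's own figure.** n = 2 × (1.960 + 0.842)² × 139² / 30² = 337 per arm. Then 337/0.76 gives 444 per arm, 1332 in all; the t-based version gives 445 and 1335. The stated 446 and 1338 are reproduced, with dropout applied as n/(1 − d).

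**2. Dilution.** With a fraction d missing in an active arm, the filled mean is (1 − d) × completer mean + d × control mean. The contrast with control is therefore (1 − d) × the completer contrast. For 30 CPM:

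| d | filled contrast (CPM) |
|---|---|
| 5% | 28.5 |
| 10% | 27.0 |
| 15% | 25.5 |
| 24% | 22.8 |
| 30% | 21.0 |

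Matching does not remove this. In simulations (446 per arm, 24% missing at random, 5 or 20 matched controls, covariate R² of 0, 0.3 or 0.6, 2,000 trials per setting) the mean estimate was 22.6 to 23.2.

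**3. Interval, equal 24% dropout, unadjusted.**
- Completers: 446 × 0.76 ≈ 339 per arm; SE = 139 × √(2/339) = 10.68; half-width 20.9; z = 30/10.68 = 2.81.
- Filled data: nominal SE = 139 × √0.76 × √(2/446) = 8.11; half-width 15.9; z = 22.8/8.11 = 2.81.
- True sampling SD of the filled contrast: 0.76 × 10.68 = 8.11, equal to the nominal SE.
- Coverage of 30 CPM: the shift is 7.2/8.11 = 0.89 SE, so coverage is Φ(0.89 + 1.96) − Φ(0.89 − 1.96) ≈ 86%. Simulation gave 86–87% unadjusted and 71–87% with baseline adjustment, depending on the assumed R² and matching.
- Type I error: 5% analytically, 4.2–6.6% in simulation.

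**4. Unequal dropout, control versus active (assumed rates).** Nominal SE is 139 × √((0.82 + 0.70)/446) = 8.11 in both cases below.
- Active 18%, control 30%: true SD = 0.82 × 139 × √(1/(446 × 0.82) + 1/(446 × 0.70)) = 8.78; type I error about 7.0%.
- Active 30%, control 18%: true SD 7.50; type I error about 3.4%.

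**5. ERS+SMS versus ERS (assumed rates).** Both arms truly +30, with 30% missing in ERS+SMS and 18% in ERS: 0.70 × 30 − 0.82 × 30 = 21.0 − 24.6 = −3.6 CPM, where the truth is zero.

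**6. LOCF.** If the effect was 30 CPM at month 4 and has gone by month 22, and every dropout was last seen at month 4, LOCF shows 0.24 × 30 = 7.2 CPM at month 22. If half of them left before month 4 and carry baseline forward, it shows 0.12 × 30 = 3.6 CPM.

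**The case against.** The strongest reply concerns the target. If people who drop out lose all benefit, the average effect over everyone randomised is itself 22.8 CPM, and the filled analysis estimates it well: simulated coverage of that value was 94%. The Background remark on unsustained gains makes this plausible. So a reader who infers that the primary estimate is biased under any circumstances goes too far; the documents do not say what dropouts' outcomes would be. What remains is that the protocol does not declare this assumption, and that the rule also covers people who were only temporarily lost.

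Other stronger readings also fail:

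- **Intervals falsely narrow, tests anti-conservative.** With equal dropout the contrast's SE is right for the shrunken estimate and type I error is held; the undercoverage comes from the shift. Single-arm SEs are too small (control mean: nominal 5.74 against true 7.55), but this cancels in the contrast. Error rates rise only when control dropout exceeds active dropout.
- **A 24% shrinkage throughout.** The 24% is one overall planning rate. It applies at most to month 22, and less to earlier visits or a time-averaged effect.
- **Proper draws were meant.** A condensed article may leave draws and pooling to the analysis plan. The word for averages argues against this reading; if it were right, the narrower-interval point would fall but the dilution would stay.
- **LOCF certain to be triggered and wrong by 7 CPM.** The trigger is likely on the planning rate, not certain, and 7.2 is an upper bound.
- **Broken blinding.** "The statistician will also be blind to group allocation until completion of the statistical analysis" does not say who performs the imputation, and coded arms could be used. This is not a finding.

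The per-protocol analysis avoids the control fill, but it selects adherent completers and so is not a sound check on it. A different method for the economic evaluation is not in itself an error in the primary effect; it is an inconsistency that needs resolving.

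**Conclusion.** The rule is wrong as written. It is labelled multiple imputation and describes a deterministic fill from one arm. If dropouts keep the completers' benefit, a 30 CPM effect is expected to appear as about 22.8 CPM at month 22 when 24% are missing there; if they keep part of it, the bias is smaller; if they keep none, there is none. Under full retention the 95% interval covers 30 CPM about 86% of the time unadjusted. For active versus control with equal dropout the error is conservative and the null is protected. For ERS+SMS versus ERS the direction depends on which arm loses more people: the −3.6 CPM rests on assumed rates of 30% and 18% and would reverse sign if they were exchanged. Neither planned sensitivity analysis settles whether the month-22 result is robust: LOCF can credit dropouts with a month-4 gain that has since gone, and the per-protocol set is selected.

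**What to change.** 1. Make one of these the primary analysis: the likelihood-based mixed model on observed data, with a covariance structure that lets a participant's visits correlate (the diagonal within-participant matrix under consideration would not do this by itself); or multiple imputation by arm using country, age, gender, SPPB, baseline and earlier outcomes, pooled by Rubin's rules.
2. Remove the control-average fill from the primary analysis. If a control-based assumption is wanted, state it and run it with proper draws as a labelled conservative sensitivity analysis.
3. Replace LOCF with delta-adjusted imputation.
4. Use one missing-data assumption for EQ-5D in the clinical and economic analyses, or explain the difference.

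The cost is protocol wording and modest programming, since chained equations by arm are already planned for the economic evaluation. The interval will be wider: on the unadjusted figures, a half-width of 20.9 instead of 15.9 CPM. The 80% power in the sample size calculation already rests on about 339 completers per arm, so nothing planned is lost.
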